## Abstract

**Background:**

The transition from high school to post-secondary education and work is difficult for adolescents on the autism spectrum. Transition planning can be an effective way of supporting adolescents on the autism spectrum to prepare for leaving school and to succeed in obtaining employment; however, there is a need for an autism-specific transition planning program with proven effectiveness. This paper describes a trial protocol for evaluating the Better OutcOmes & Successful Transitions for Autism (BOOST-A™); an online interactive program that empowers adolescents on the autism spectrum to plan their transition from school to further study, training, or employment.

**Methods:**

The trial will involve adolescents on the autism spectrum in high school and their parents, who will be alternately assigned to a control group (regular practice) or an intervention group (using the BOOST-A™). The BOOST-A™ was developed using the PRECEDE-PROCEED model, and is based on the self-determination model, and the strengths- and technology-based approaches. It involves participants completing a series of online modules. The primary outcome will be self-determination, because high self-determination has been linked to successful transition to employment among adolescents on the autism spectrum. Secondary outcomes will include domain-specific self-determination, career planning and exploration, quality of life, and environmental support. Data will be obtained from questionnaires completed by the adolescent on the autism spectrum and their parent/s. Data collection will take place at baseline (Time point 1) and 12 months later (Time point 2).

**Discussion and conclusions:**

This trial will provide evidence of the effectiveness of the BOOST-A™ to assist adolescents on the autism spectrum to successfully transition from school.

*Trial registration* #ACTRN12615000119594

## Background

People on the autism spectrum experience difficulties with socialization and communication, as well as restricted interests and repetitive behaviours [1]. The term ‘people on the autism spectrum’ is the one of the preferred terms by members of the autism community [2] and describes people with a diagnosis of autism spectrum disorder, as defined by the Diagnostic and Statistical Manual of Mental Disorders, fifth edition (DSM-5) [1]. This includes individuals with Asperger’s syndrome and pervasive developmental disorder—not otherwise specified, as previously delineated in the DSM-4 [3]. The transition from school to post-school activities is difficult for adolescents on the autism spectrum [4, 5], who are significantly less likely to attend post-secondary education and training than young people with other disabilities [6]. People on the spectrum who have an intellectual ability within or above the average range have difficulty securing employment; only 16% in Australia have full-time employment after leaving school and 33% work part-time [7]. In addition, adolescents on the autism spectrum are three times less likely to participate in vocational activities compared to their peers on the autism spectrum who also have an intellectual disability (ID) [8].

A lack of transition planning can contribute to poor post-school outcomes for adolescents on the autism spectrum [6]. Transition planning involves the setting of personal goals to prepare the adolescent for leaving high school. Transition planning has been linked to improved self-determination, increased rates of employment, improved success in post-secondary education, and higher community participation among adolescents with disability [9]. Unfortunately, current transition planning practices have resulted in inferior outcomes for adolescents on the autism spectrum when compared to adolescents with other disabilities [10]. Only 23% of adolescents with autism are involved in transition planning [11]; and even when they are involved, they are less likely to be active participants in the process. Fewer parents of adolescents with autism perceive the transition planning process as useful [11], and have reported that they want to be more involved in the process [10, 12]. Currently, schools tend to focus on the academic performance of adolescents on the autism spectrum who do not have an ID, rather than engaging them in comprehensive transition planning [13]. In addition, autism-specific challenges are often not taken into consideration. These include difficulties conceptualizing hypothetical future events, managing anxiety, and communicating their preferences to others [13]. Therefore, there is a need for a more tailored transition planning program for students with autism.

Further to this, there is a need for a transition planning program that has proven effectiveness [14]. Current generic transition planning programs have little empirical evidence to prove their efficacy [15] and many focus on limited aspects of transition planning [16–18]; failing to provide an overall guide for adolescents and their parents on how to navigate the entire transition planning process. There is a need for an accessible and tailored transition planning program for adolescents on the autism spectrum that is proven to be effective in improving their self-determination.

This paper describes a trial protocol for the development and evaluation of a transition planning program called the Better OutcOmes & Successful Transitions for Autism (BOOST-A™). The BOOST-A™ aims to target the specific needs of adolescents on the autism spectrum, to empower them to plan their transition from school to further study, training or paid/unpaid work. This trial follows principles of the SPIRIT guidelines for protocols that support high-quality conduct and reporting of clinical trials [19].

### Objectives of the trial

The hypothesis for the trial is that the BOOST-A™ will improve self-determination in adolescents on the autism spectrum transitioning to post-school life. The objectives of the trial are to:determine the effectiveness of the BOOST-A™ in improving self-determination in adolescents on the autism spectrum; anddetermine the effectiveness of the BOOST-A™ in improving quality of life; access to environmental supports; career planning and exploration; and vocational exploration among adolescents on the autism spectrum.

## Methods

### PRECEDE-PROCEED model

The PRECEDE-PROCEED model [20] was used to guide the development and evaluation of the BOOST-A™. The model provides a stepwise guide to developing evidence-based interventions that meet the needs of the target group [21]. The model has been used to develop previous health interventions [22, 23]. The PRECEDE component guides the development of an intervention through the application of available research and an appropriate theoretical framework [20], and was used in the development of the BOOST-A™. The PROCEED component provides guidance on trialing and evaluating an intervention, and was used to structure the trial of the BOOST-A™.

### Theoretical frameworks

The BOOST-A™ was based on three main theoretical frameworks: the self-determination model, a strengths-based approach, and a technology-based approach.

#### Self-determination model

Self-determination is an individual’s ability to direct their own life; that is, to make choices about the pathway they will take without feeling they have to rely heavily on others [24]. Self-determined people are goal-orientated, have strong problem-solving abilities, and know their strengths and weaknesses. The environment plays a pivotal role in the development of a young person’s self-determination, with the greatest environmental influences being their family, school, and the wider community [25]. Self-determination is influenced by an individual’s sense of autonomy, competence and relatedness; all of which impact on intrinsic motivation [26]. Self-determination can be fostered by incorporating four key facets: promotion of self-knowledge; consistent support between family, school and professionals; opportunities to take risks; and supporting reflective practice [27].

Self-determination has particular importance for people with a disability, because it is a predictor of successful transition into an autonomous adult life, and is crucial to living an empowered life [25, 27–29]. People with developmental disabilities who feel a greater sense of control in their lives are more likely to be employed in the regular workforce [30]. Therefore, the model of self-determination was used to underpin the development of the BOOST-A™.

#### Strengths-based approach

A strengths-based approach advocates focusing on the individual’s strengths, as opposed to the focus on deficits that is often associated with the medical model [31]. The strengths-based approach was developed in the 1980s to challenge the paradigm that disability is a weakness and a fundamental flaw in the individual, and that individuals were to blame for their difficulties [32]. In contrast, a strengths-based approach views the individual as an asset to society and focuses on how the community can support them to leverage their talents, rather than on how the individual can change to meet society’s expectations. The strengths-based approach is being increasingly utilized by many health professionals [33], as well as in the career development arena [34]. In addition, families with children on the autism spectrum who focused on their child’s strengths had a more positive view of disability and described their child as being more resilient [35]. Thus, the strengths-based approach was used in developing the BOOST-A™.

#### Technology-based approach

Technology-based interventions for individuals on the autism spectrum are growing in popularity [36]. A meta-analysis of technology-based training for people with autism supported the effectiveness of these interventions and advocated their use with this population [37]. Furthermore, parents and students with developmental disabilities who used technology in transition planning were significantly more satisfied with the outcomes of the planning process and experienced increased self-determination [16]. The use of technology-based interventions could be particularly relevant for people on the autism spectrum, as they often have an interest in, and aptitude for, technology [38]. An online program also has the potential to increase accessibility to the transition planning process, especially for adolescents and their families living in regional or remote areas. Therefore, a technology-based approach was used for the development of the BOOST-A™.

### Needs assessment

As recommended by the PRECEDE model, a needs assessment was completed to determine the priority areas in transition planning for adolescents on the autism spectrum [20]. The needs assessment encompassed a range of information sources and included both quantitative and qualitative data, as recommended in the literature [39]. The needs assessment involved two phases: (i) a survey of the adolescents on the autism spectrum, their parents and the professionals who work with them; and (ii) interviews with the parents and professionals. In addition, a systematic review was completed to appraise career planning tools for use with individuals on the autism spectrum [40], and a comprehensive literature review was conducted to identify current best-practice in transition planning.

The findings of the literature review and the needs assessment shaped the transition planning objectives for adolescents on the autism spectrum (Fig. 1). The objectives consisted of three guiding ideals and five strategies to direct the overall development of the BOOST-A™. The ideal of ‘Promote the big picture’ is particularly important for adolescents on the autism spectrum, as it advocates the importance of assisting adolescents to understand what life will be like after school. Adolescents with autism may not implicitly understand the ‘big picture’ due to difficulties with abstract thought [41], which may cause them to less motivated to take part in transition planning. Therefore, assisting adolescents on the autism spectrum to understand the ‘big picture’ may enhance their motivation and participation in transition planning. The full findings of the needs assessment are reported elsewhere [42].

**Fig. 1 Fig1:**
[figure not shown]
Transition planning objectives for adolescents on the autism spectrum

### The intervention: BOOST-A™

Using the transition planning objectives for adolescents on the autism spectrum (Fig. 1), the primary researcher (MH) developed the BOOST-A™. The BOOST-A™ was written in plain language at a year five reading level. This reading level has been recommended as being appropriate to disseminate health communication materials to the community, including low-literacy readers [43]. Feedback was obtained by a community reference group comprised of young people on the autism spectrum, parents and professionals throughout the development of the BOOST-A™ to ensure it met the needs of adolescents on the autism spectrum.

The BOOST-A™ is delivered in four online modules with an introduction via a website that requires a login. Table 1 shows the objectives addressed in each module. Each of the BOOST-A™ modules contains interactive cartoon videos that explain to the adolescent the overall purpose of transition planning, as well as the aim of each module. This links back to the guiding ideal identified in the needs assessment of ‘promote the big picture’.

**Table 1 Tab1:** BOOST-A™ overview

Module	Description	Who and where	Objectives addressed
Introduction	Information about the process and what to expect in the program, and why it is important to engage in transition planning from an early age	Adolescent and their parent/s at home	1, 2, 4
1. About Me	Six activities to identify the adolescent’s interests, strengths, work preferences, training goals, life skills and learning style	Adolescent and their parent/s at home	2, 3, 4, 5
2. My Team	Guides how to identify a team of people to support the adolescent in their transition planning, and how to book the first team meeting. Adolescents choose how they want to get involved in the team meetings, with graded prompts provided	Adolescent and their parent/s at home	2, 4, 5
3. First Meeting	Guides the first meeting; when the team are provided with recommendations for job areas and goals based on the adolescent’s strengths and evidence from the literature	Adolescent, their parent/s and their team at the first meeting	2, 3, 4, 5
4. My Progress	Guides the progress meetings; when the team review how the adolescent’s goals are progressing; and discuss positive learning experiences	Adolescent, their parent/s and their team at subsequent team meetings	2, 3, 4, 5

The first module is ‘About Me’, in which the adolescent completes a number of activities to identify their interests and strengths. The focus is on leveraging the adolescent’s strengths, rather than focusing on their weaknesses [32]. The second module is ‘My Team’, which assists the adolescent and their parents to identify people who may support them in their transition planning journey. Being actively involved in transition planning and having people who provide tangible assistance and encouragement is pivotal to promoting self-determination [44, 45]. Therefore, this module encourages and supports the adolescent to become an integral and active member of the team. The third module, ‘First Meeting’, guides the team to develop goals; providing recommendations for goals that are based on the adolescent’s strengths and best-practice recommendations from the research literature, such as the importance of engaging in real life experiences [9]. The fourth module, ‘My Progress’, is completed by the team at all subsequent team meetings to review how the adolescent’s goals are progressing. This module encourages the team to reflect on progress in a positive manner and to view all experiences as learning opportunities, rather than failures.

### Pilot studies

Two pilot studies were conducted to determine the feasibility of the BOOST-A™, and to provide formative and process feedback. The pilot studies were:Pilot A: with adolescents on the autism spectrum, their parents, teachers and other professionals; andPilot B: with allied health professionals.

*Pilot A* consisted of adolescents on the autism spectrum (n = 6), their parents (n = 6) and the professionals who worked with them (n = 12); who were recruited using convenience sampling from a database of people who had registered their interest in  the research project. Participants were asked to use the BOOST-A™ along with their team and to provide feedback on the process. All participants rated the BOOST-A™ as helpful, realistic and relevant (100%). Participants rated the ‘My Team’ section as low for usability (50%), and provided recommendations for improvement.

*Pilot B* included 88 allied health professionals, including speech pathologists (n = 26), psychologists (n = 29) and occupational therapists (n = 29) registered to practice in Australia, and recruited through allied health forums and professional networks. Participants completed an online survey comprised of questions about whether the BOOST-A™ was helpful, realistic, meaningful, relevant, and clear. Approximately three out of four (76%) of the allied health professionals rated the BOOST-A™ as appropriate, usable, and feasible; and 84% reported they would use BOOST-A™ in the future. Participants identified three main areas for improvement: (i) verbose language, (ii) need for support from parents in the ‘About Me’ section, and (iii) need for guidance overall in the program; and provided suggestions for improvement.

Based on feedback from both pilots, the BOOST-A™ was modified to enhance usability of the program, with the conversion from a Java platform to a web-based program that allowed for improved navigation and increased use of graphics and animations, and an overall reduction to the length of the program. The full results from these pilot studies are reported elsewhere [46].

### Trial design and procedures

A controlled clinical trial [47] will be used to determine the effectiveness of the BOOST-A™ in improving the self-determination of adolescents on the autism spectrum; and in improving their outcomes of quality of life, access to environmental supports, and career planning skills. The trial will be a cluster group, two-arm, superiority trial with 1:1 allocation ratio. The trial will aim to detect any difference in these outcomes between participants in the intervention group (BOOST-A™) and a control group. Figure 2 shows the schedule of enrolment, intervention, and assessment for the trial. Participants in the intervention group will complete the BOOST-A™ at home and/or at school. Participants will complete the BOOST-A™ over a period of 12 months. This timeframe was chosen to ensure the participants have adequate time to complete all four modules, including the initial team meeting and at least one review meeting. Adherence will be monitored via website analytics, including number of modules completed and number of logins to the BOOST-A™ website. Participants allocated to the control group will participate in the existing post-school planning process used at their school (regular practice).

**Fig. 2 Fig2:**
[figure not shown]
Schedule of enrolment, intervention and assessments

#### Participants

##### Identification and recruitment

Potential participants will be recruited via social media and community organization websites, flyers, and posters located in services for people on the autism spectrum. Community organizations, health professionals, and schools will be asked to email any potential participants directly. Recruitment material will consist of a flyer outlining the inclusion criteria and requirements of the trial. The flyer will request prospective participants to contact the primary researcher (MH) directly via email or telephone to register their interest in the trial. At the initial contact, each potential participant will be screened by MH for eligibility, and they will be sent the electronic participant information form and a link to an online consent form.

##### Inclusion and exclusion criteria

Inclusion criteria for participating in this trial are as follows:Adolescents diagnosed with Autism spectrum disorder, as defined by the diagnostic and statistical manual of mental disorders, fifth edition (DSM-5) [1] or the fourth edition (DSM-4) [3];Living in Australia;Able to read and write in English at a year five reading level;Enrolled in years 8–11 at school (including mainstream, special education or home-schooling programs); andPossess basic computer skills to enable use of the online BOOST-A™.

Adolescents will have a formal diagnosis of autism prior to participating in this trial. Diagnosis will be verified by the Social Responsiveness Scale-Second Edition (SRS-2) [48]. The SRS-2 is a diagnostic screening tool, and has been used in previous trials to verify diagnosis [49, 50]. Whilst it would be preferable to have used the autism diagnostic observation schedule (ADOS) [51] for diagnosis, it is not possible for the researchers to administer this 60 min assessment in person given the wide geographic distribution of participants across Australia. Further verification of diagnosis will be provided by parent report, as previous studies have verified the validity of diagnostic information reported by parents [52]. Exclusion criteria will be if the adolescent on the autism spectrum has an ID, as this will limit their ability to use the program, or if the student is enrolled in another transition planning program. Whilst it would have been ideal to complete an assessment of cognitive functioning for each participant, this is not feasible as the sample will be recruited from across Australia and the trial will be completed only online.

##### Treatment allocation

Following initial screening, potential participants will be allocated to either the intervention or control group according to the order in which they register interest. The first participant will be allocated to a group based on a coin toss completed by a researcher who will not be directly involved in liaising with participants. The exception to this allocation scheme is that if a newly enrolled participant is attending a school that a previously or currently enrolled trial participant attends, then the newly enrolled participant will be allocated to the same treatment group as the previous student. The reason for this is to reduce the risk of contamination, since school staff will be involved in administering the intervention. Participants will be blinded to their treatment; however, non-blinded allocation and lack of randomization could introduce potential bias. Once allocated to a group, participants will be sent the participant information and consent form. Forms for the intervention group will differ slightly from those for the control group, as they will contain information about the BOOST-A™, to ensure blinding to treatment is maintained. Participants who provide written consent will then be assigned a unique participant identification number. A strength of the trial is that the BOOST-A™ will be administered by parents and professionals who are not a part of the research team, thereby minimizing researcher bias. In addition, the primary researcher will have minimal information about the participants at time of randomization.

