#### Data collection

Outcome data will be collected via an online survey using Qualtrics software (Version 2016). The survey containing the outcome measures for the trial will be emailed to participants at two data collection points: at baseline (Time point 1), and 12 months later (Time point 2). Participants will complete the online survey in their own environments, which could be home, work, or school. Demographic information will be collected from parents at Time point 1. This information will include the adolescent’s age, gender, year level at school, and their residential postcode (to determine socioeconomic status). It is anticipated that completing the online outcome measures will take 30–45 min each time. Participants will be given a leeway of two months after each scheduled data collection point to complete the outcome measures. Participants will be reminded, as needed, by the primary researcher via telephone and email to complete the outcome measures. The trial commenced on 26 November 2015 (Time Point 1), and data collection for the post-measures began on the 26 November 2016 (Time Point 2).

The Social Responsiveness Scale-Second Edition (SRS-2) [48] will be used to classify autism severity. Parents will complete the School Age Rating Form, which is designed for children aged 4–18 years. The SRS-2 consists of 65 items and can be administered in 15–20 min. The scale results in a total score and a *t*-*score*, which can be used as an index of severity of social deficits on the autism spectrum. Scores can be interpreted as falling into one of the following four categories: within normal limits, mild deficit, moderate deficit, and severe deficit. The scale has been standardized using a nationally representative sample, and has strong psychometric properties including high internal consistency (α = .95); construct validity (two strong factors); test–retest reliability (*r* = .88–.98); and interrater reliability (*r* = .91 between mothers and fathers) [48]. Studies have shown that the SRS-2 can detect clinically meaningful and statistically significant differences between typically developing children and those diagnosed with autism [54]. Additional independent variables for this trial will be comorbidities (including mental health), gender, age, and socioeconomic status.

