### Ethics, consent and permissions

Ethics approval to conduct this trial has been obtained from Curtin University Human Research Ethics Committee (approval number HR110/2014), and the Catholic Education Offices and Departments of Education in Western Australia, Victoria, Queensland, New South Wales, Tasmania and South Australia. Written informed consent will be obtained from all adult participants. Participants under 18 years of age will provide informed written assent, and their parents will provide informed written consent for their participation. Principals of the schools attended by participants in the intervention group will provide informed written approval for their staff to use the BOOST-A™; consent is not required by this group because the teachers are not taking part in data collection. Participants in the control group will be offered the opportunity to use the BOOST-A™ once the trial is complete, if it is proven to be effective in achieving the trial objectives.

The trial design and procedures will adhere to the National Statement on Ethical Conduct in Human Research [71] and the Australian Code for the Responsible Conduct of Research [72]. The trial is registered with the Australia and New Zealand Clinical Trial Registry (#ACTRN12615000119594). The trial was developed according to the Consolidated Standards of Reporting Trials (CONSORT) 2010 guidelines [73].

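### Allocation by alternation is predictable and comes before arm-specific consent, so selection can differ by arm, and the text wrongly speaks of randomization

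*Protocol article*

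**What the plan says.** The abstract describes adolescents and parents "who will be alternately assigned to a control group (regular practice) or an intervention group (using the BOOST-A™"). The Treatment allocation section gives the mechanism: after initial screening, "potential participants will be allocated to either the intervention or control group according to the order in which they register interest". The only chance element is at the start: "The first participant will be allocated to a group based on a coin toss completed by a researcher who will not be directly involved", meaning someone with no contact role towards the families. A pupil whose school already has a participant joins that participant's arm, to limit contamination.

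Under Identification and recruitment, families register with the primary researcher by email or telephone. The same researcher screens them at first contact, after which "they will be sent the electronic participant information form and a link to an online consent form". Treatment allocation places the forms later: "Once allocated to a group, participants will be sent the participant information and consent form". The intervention arm's forms carry BOOST-A information that the control forms do not, and this is justified as protecting blinding. An identification number follows only after written consent.

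The same section concedes that allocation is not blinded and not randomized, and that this may cause bias. It then closes its list of strengths by saying that "the primary researcher will have minimal information about the participants at time of randomization".

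**The concern.** Random, concealed allocation makes the arms comparable on factors nobody measured. Alternation by registration order lacks that protection in two places.

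First, whoever takes registrations in order can tell which arm comes next while judging eligibility. Several criteria leave room for judgement over the telephone, notably reading level, basic computer skills and absence of intellectual disability without cognitive testing.

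Second, families decide on consent after allocation, using a form that differs by arm. A motivated family may accept a form describing a new program and decline one describing usual practice. Motivation could plausibly predict how much self-determination, the primary outcome, improves over 12 months.

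The stake is whether a between-arm difference in change on the AIR scale can be attributed to BOOST-A. A reader who takes the word randomization at face value would credit the trial with a protection it does not have.

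**Working it through.** The plan gives no figure for this point, so the check is mainly a reading of the text, with two short calculations.

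**Predictability.** Inputs: one coin toss for the first participant and a fixed rule afterwards (Treatment allocation); a minimum total of 80, 40 per arm (Sample size).
- Allocations fixed by rule: 80 − 1 = 79 of 80. If some allocated families decline, more than 80 are allocated, and it remains all but one.
- Expected correct guesses by someone who knows the rule and the previous allocations: (79 + 0.5)/80 = 99.4%, against 50% under simple randomization.
- The same-school rule does not restore uncertainty, because the arm of such a pupil is known once the school is known.

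**Who can foresee the arm.** Registrations go to the primary researcher, who also screens, and the protocol calls allocation non-blinded. The independent coin-tosser conceals only the first allocation. That the primary researcher knows the next arm is not stated, but it follows closely from these three facts. Holding minimal information is weak reassurance about someone who has just checked diagnosis, year level, reading level and computer skills.

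**Order of steps.** Treatment allocation gives: screen, allocate, send arm-specific forms, consent, identification number. Arm-specific forms require allocation first. Identification and recruitment mentions the forms immediately after screening and says nothing of allocation. The two sections can be read as one sequence, but the order should be stated once. That baseline follows allocation is an inference from consent following allocation.

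**What the planned analysis repairs** (Statistical analysis section).
- Intention-to-treat, with Time point 1 values carried forward, keeps everyone who supplied baseline data. It cannot recover families who declined after seeing their form.
- Change scores remove stable differences between the arms, but not selection related to how much a pupil improves.
- Adjustment by general linear model applies only if baseline differences are found, and only to measured variables.

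**Illustration of consequence (assumed sizes).** Let b be the between-arm difference in mean change caused by selection alone, in SD of the change score. Take 40 per arm, independent observations, a two-sided 5% test and no true effect.
- SE = √(2/40) = 0.2236.
- Rejection probability = 1 − Φ(1.96 − b/SE) + Φ(−1.96 − b/SE).

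| b (SD) | b/SE | Rejection probability |
|---|---|---|
| 0 | 0 | 0.0500 |
| 0.1 | 0.447 | 0.0732 |
| 0.2 | 0.894 | 0.1455 |
| 0.3 | 1.342 | 0.2687 |

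The document supplies no value of b. The table shows sensitivity and is not an estimate.

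**The case against.** The strongest reply is that the authors have been open. The abstract says participants are alternately assigned, the design section says controlled clinical trial and not randomised trial, and Treatment allocation names the risk of bias. That stands, and a reader should not infer that the protocol passes itself off as a randomised trial. Disclosure, however, does not restore comparability, and the word randomization still sits in a list of strengths.

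A second reply is timing. The trial began on 26 November 2015 and Time point 2 collection on 26 November 2016, so enrolment may be closed. That limits the design remedy but leaves labelling, reporting and interpretation.

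Third, separate forms serve the stated blinding. This is a real cost of moving consent ahead of allocation and must be weighed.

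Some stronger readings are tempting, but the document does not support them:
- From "Participants will be given a leeway of two months after each scheduled data collection point to complete the outcome measures" a reader might infer that intervention baselines are taken after BOOST-A use has begun. The leeway applies to both arms, no text opens access before baseline, and the schedule figure is not shown.
- From "Principals of the schools attended by participants in the intervention group will provide informed written approval" a reader might infer an enrolment gate in one arm only. The approval is for staff to use the program. It is not made a condition of participation, the program may be completed at home, and home-schooled pupils are eligible.
- A reader might put a figure on the bias from a guessed refusal rate and a guessed difference in 12-month scores. The planned analysis is of change, from which stable differences largely drop out, so such a figure would not be the bias in the planned estimate.

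**Conclusion.** The concern holds. By the protocol's own account, every allocation after the first is predictable and arm-specific consent follows allocation. Reference to the time of randomization contradicts the admission, in the same section, that there was none. Foreknowledge by the screener is very probable but inferred. The document does not show that selection differed by arm, only that the procedure allows it and the analysis would not correct it. The size and direction of any bias are unknown. Under the stated assumptions, even 0.1 SD of selection in the change score raises the false-positive rate from 5% to about 7%, and 0.3 SD raises it to about 27%. Because allocation underlies the causal claim on the primary outcome, the description and the reporting need correcting even if recruitment is over.

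**What to change.** **For any remaining enrolment.** Allocate each new school from a concealed, computer-generated permuted-block list held by the researcher who does not liaise with participants. Later pupils follow their school, as now. Reveal the arm only after eligibility is confirmed and, where compatible with the stated blinding, after consent and baseline.

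The list costs almost nothing. The downside is that consent wording must be reworked so that controls remain unaware of BOOST-A details. Pupils joining a school already allocated would still have a known arm, which is the price of the contamination rule.

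**For those already enrolled.**
- Describe the trial as non-randomised, with allocation by alternation.
- In the last sentence of Treatment allocation, replace randomization with allocation.
- State once, consistently across Identification and recruitment and Treatment allocation, when forms are sent relative to allocation.
- Report by arm the numbers allocated, consented and completing baseline. Report the numbers registered and eligible by the arm assigned or next due.
- Limit causal conclusions on the primary and secondary outcomes accordingly.

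These are wording changes and counts, provided screening and refusals were logged. The cost is a less favourable description of the trial.

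Do not add an analysis that excludes participants according to their first BOOST-A login. Controls have no logins, so it would remove participants from one arm only and create the kind of selection at issue.
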